#### Risk stratification

Risk stratification will be applied to all children in the full sample. Based on information from the PRN regarding the pregnancy (weeks gestation) and the newborn (birth weight, Apgar score and congenital malformations), the children of the full sample will be assigned to a risk profile (i.e. 'low risk', 'moderate risk' or 'high risk'). The risk stratification criteria are: 1) prematurity (< 37 weeks gestation); 2) 5-minute Apgar score (< 7); 3) congenital malformations; and 4) birth weight (< 2,000 gram) (see figure 1). The criteria are set such that the probability of a false negative, i.e. the chance that a child 'at risk' is assigned to the low risk category, is minimized. A child will be assigned to the 'moderate risk' category if the child is born before 37 weeks gestation, has a Apgar score below seven, or has a congenital malformation. If the child also has a birth weight below 2,000 gram, the child will be assigned to the 'high risk' category. The other children will be assigned to the 'low risk' category. Based on figures reported by the PRN [12] and expert opinion it is expected that approximately 8% of the singletons will be assigned to the 'moderate risk' or 'high risk' category. All 'moderate risk' and 'high risk' singletons and a random selection of 10% of the remaining ('low risk') singletons will be included in the base sample. Based on figures reported by the PRN [12] and expert opinion it is expected that half of the twin children is born before 37 weeks gestation, have a low APGAR score or a congenital malformation. Approximately 40% of these twin children will also have a low birth weight (20% of all twin children) and will be assigned to the 'high risk' category. The other 60% of these twin children will have a birth weight above 2000 gram (30% of all twin children) and will be assigned to the 'moderate risk' category [12]. All other children (50% of all twin children) will be assigned to the 'low risk' category. All twin children of the 'high risk' category, a random selection of 30% of the 'moderate risk' category and a random selection of 10% of the 'low risk' category will be included in the base sample.

#### Empirical data collection up to the first year of life

Data with respect to the first year of life will be collected in children of the base sample. Based on figures reported by the PRN over 2004 [12] and expert opinion it is expected that approximately 1,278 children will be included in the base sample. The estimated number of children in each risk category is shown in figure 1.

Cost and outcome data up to the first year of life will be obtained from the hospital information systems of the relevant hospitals, existing registries and, if necessary, patient charts will be reviewed to obtain relevant cost and outcome data. The following registries will be used: 1) the PRN, which encompasses information regarding mother, pregnancy and the newborn; 2) the National Medical Registration (LMR), which registers medical and administrative data of all patients who have been admitted or have received outpatient treatment in Dutch hospitals; and 3) the Netherlands Twin registry (NTR), which follows a cohort 72,000 twins regarding pre- and perinatal information, health status, growth and motor development and behaviour [53,54]. As we intend to collect follow up data directly from hospital records, the use of data from the LMR will be optional. It is expected that data collection up to the first year of life will succeed in 90% of these children.

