## Methods/Design

### Design

A retrospective multi-centre (n = 5) cohort study will be performed, in which a representative sample of IVF twin children will be compared with a representative sample of IVF singletons with respect to mortality, health outcomes, HRQoL and costs from birth up to five years of life. Subsequently, future costs and health outcomes up to 18 years of life will be modelled. Input for the model will be based on the empirically collected data up to five years of life, existing databases, literature and expert opinion.

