#### Empirical data collection from the first year of life up to the fifth year of life

Based on empirical collected costs and outcome data up to the first year of life, a subgroup of children will be selected for data collection up to the fifth year of life, referred to as the reduced sample. All children with resolved or persistent health problems, and a random sample of children without resolved or persistent health problems will be included in the reduced sample. Assuming that missing data are completely at random, resolved and persistent health problems are expected in 4.0% of the singletons and in 12.5% of the twin children. Approximately 488 children will be included in the reduced sample (see figure 1). Besides the data sources mentioned above, cost and outcome data up to the fifth year of life will also be gathered by means of a parent questionnaire. The questionnaire will consist of three parts, the first part referring to the past, the second part referring to the present and the third part referring to expectations regarding the future. The parent questionnaire will focus on health outcomes, HRQoL and costs.

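### A registry that follows only twins is a named source for outcomes up to age five, so detection of health problems can differ between twins and singletons

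*Protocol article*

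**What the plan says.** The *Design* section sets up a comparison of IVF twin children with IVF singletons "with respect to mortality, health outcomes, HRQoL and costs from birth up to five years of life".

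The first-year sources are stated as follows: "Cost and outcome data up to the first year of life will be obtained from the hospital information systems of the relevant hospitals, existing registries". Chart review is added where needed. Three registries are then listed for use:

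- the Perinatal Registry Netherlands (PRN), which covers mother, pregnancy and newborn;
- the National Medical Registration (LMR);
- "the Netherlands Twin registry (NTR), which follows a cohort 72,000 twins regarding pre- and perinatal information, health status, growth and motor development and behaviour".

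Only one of the three is left open: "the use of data from the LMR will be optional".

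For years one to five: "Besides the data sources mentioned above, cost and outcome data up to the fifth year of life will also be gathered" through a parent questionnaire. The NTR therefore stays among the sources to age five. Its role in the 18-year estimation (a matched sample of 250 18-year-old twin children) is described separately, in *Data estimation up to the 18th year of life*.

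First-year findings decide who is followed further, and so who forms the reduced sample, by this rule: "All children with resolved or persistent health problems, and a random sample of children without resolved or persistent health problems will be included".

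**The concern.** In a cohort comparison, the means of finding an outcome should not depend on the exposure. Here the exposure is being a twin, and one listed source can exist only for twins. It covers health status, growth, motor development and behaviour, and *Outcome measures* includes developmental and behavioural outcomes. In the first year a singleton has the PRN, hospital systems or charts and, optionally, the LMR. A mild motor or growth problem that never reached a hospital could be recorded for a twin in the NTR and missed for an otherwise identical singleton.

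Two things are at stake. One is the twin-versus-singleton comparison of morbidity and development. The other is the make-up of the twin group with health problems, because first-year status gives certain entry to the reduced sample. *Problem definition* commits the study to estimates that take account of sources of bias, and this source is not dealt with in the analysis section.

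**Working it through.** **1. The plan's own figures.** These reproduce, and the point does not disturb them.

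- Base sample, singletons: 3,789 × 0.95 × (0.08 + 0.92 × 0.10) = 619.1 (stated 619).
- Base sample, twin children: 2 × 1,020 × 0.95 × (0.20 + 0.30 × 0.30 + 0.50 × 0.10) = 658.9 (stated 659). Total 1,278.0 (stated 1,278).
- Reduced sample, singletons: 3,599.55 × 0.04 × 0.90 + 56/0.80 = 129.6 + 70 = 199.6 (stated 200).
- Reduced sample, twin children: 1,938 × 0.125 × 0.90 + 56/0.80 = 218.0 + 70 = 288.0 (stated 288). Total 487.6 (stated 488).

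**2. Sources side by side.**

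| Source | Twins | Singletons |
|---|---|---|
| PRN (birth data) | yes | yes |
| Hospital systems, charts | yes | yes |
| LMR (optional) | yes | yes |
| NTR | yes | no |
| Parent questionnaire (after first-year selection) | yes | yes |

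**3. Size if an NTR entry alone can count as a problem.** Let s be the share of true problems found by the shared sources, c the share of study twins in the NTR, and r the share of otherwise missed problems that the NTR finds. Then:

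apparent ratio = true ratio × [s + (1 − s) × c × r] / s

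The documents give none of s, c or r; all values below are assumptions. With a true ratio of 1:

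| s | c | r | Calculation | Apparent ratio |
|---|---|---|---|---|
| 0.95 | 0.3 | 0.25 | 1 + 0.00375/0.95 | 1.00 |
| 0.90 | 0.3 | 0.25 | 1 + 0.0075/0.90 | 1.01 |
| 0.80 | 0.5 | 0.50 | 1 + 0.05/0.80 | 1.06 |
| 0.80 | 1 | 0.80 | 1 + 0.16/0.80 | 1.20 |
| 0.60 | 1 | 0.80 | 1 + 0.32/0.60 | 1.53 |

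For scale, the plan states that "resolved and persistent health problems are expected in 4.0% of the singletons and in 12.5% of the twin children", a ratio of 12.5/4.0 = 3.125. If a ratio of that size were observed, the true ratio behind it would lie between 3.125/1.53 = 2.04 and 3.125/1.004 = 3.11 under the same assumptions.

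**4. Whether the planned adjustments remove it.** Under *Empirical data* in the analysis section, the proportions of high, moderate and low risk children are restored to those of the original population. The categories rest on gestation, Apgar score, malformations and birth weight from the PRN. If detection inflates the twin rate p_j in each category j by a factor k, the weighted rate is Σ w_j × k × p_j = k × Σ w_j × p_j, so k remains. The one explicit bias check compares PRN data of children with and without missing data. It concerns which children are missing, not which sources each group has.

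**The case against.** The strongest reply is that harm needs a rule the article does not state: that an NTR entry alone is enough to classify a child. The article intends to collect follow-up data directly from hospital records, which both groups share. The only linkage it describes for study children is to the PRN, and the only NTR use it spells out is the matched 18-year sample. A condensed article may leave the case definition and order of sources to the full protocol. This makes the bias conditional. It does not remove the point, because the article itself names the NTR for use in the first year, makes only the LMR optional and carries the sources forward.

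Four stronger readings are tempting, and the documents do not support them:

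- **That the comparison is biased against twins as a matter of fact.** The direction is likely, not certain. NTR data might mainly fill gaps for healthy twins whose hospital data are missing.
- **That twin costs in the first year are inflated.** Costs are resource volumes times unit prices, and the NTR is not described as holding resource use. QALYs come from mortality and parent-rated EQ-5D and HUI3, so they are not directly touched either.
- **That the gap is as wide at age five as at age one.** The parent questionnaire is not restricted to twins and can pick up problems in singletons that never reached a hospital. It narrows the gap after the first year. It cannot do so for first-year status, which is assigned before the questionnaire is used.
- **That altered selection must make twins look worse in later follow-up.** Selecting flagged children with certainty is not biasing in itself if the weights reflect actual selection. Mild NTR-only cases would also lower average severity in the twin group with problems.

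**Conclusion.** The point holds in conditional form. As written, the plan allows a twin-only source to feed outcomes compared between twins and singletons, and nothing in the analysis section corrects for it. If NTR entries count, apparent twin morbidity is probably inflated, chiefly for growth, motor and behavioural items and for first-year health-problem status. The set of twins entering the reduced sample as having problems also changes.

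The size cannot be derived from the documents. The range of about 1.00 to 1.5 rests on s from 0.60 to 0.95, c from 0.3 to 1, r from 0.25 to 0.8, equal true risk, and a problem counting when any source shows it. The effect is negligible if shared hospital records find nearly everything. The sample sizes are unaffected, and no effect on costs is shown. It is worth changing because the remedy is simple and removes the dependence on these unknowns.

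**What to change.** - Define first-year health-problem status, and so entry to the reduced sample, only from sources available for both groups: PRN, hospital systems and charts, and the LMR if it is used for both. The parent questionnaire cannot be part of this definition, because it is described only for the stage after that status has selected the children.
- Base the main twin-versus-singleton comparison of outcomes up to age five on those sources plus the parent questionnaire.
- Keep NTR data for twin-only description, for validating the shared sources in twins, for the 18-year extrapolation, or for a sensitivity analysis that adds them to the main comparison.

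This takes wording in the two data-collection sections and the analysis section, with no new data collection. It sets the factor due to unequal sources to 1.00. The cost is slightly less detail on twins in the main comparison.

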#### Empirical data collection from the first year of life up to the fifth year of life

Based on empirical collected costs and outcome data up to the first year of life, a subgroup of children will be selected for data collection up to the fifth year of life, referred to as the reduced sample. All children with resolved or persistent health problems, and a random sample of children without resolved or persistent health problems will be included in the reduced sample. Assuming that missing data are completely at random, resolved and persistent health problems are expected in 4.0% of the singletons and in 12.5% of the twin children. Approximately 488 children will be included in the reduced sample (see figure 1). Besides the data sources mentioned above, cost and outcome data up to the fifth year of life will also be gathered by means of a parent questionnaire. The questionnaire will consist of three parts, the first part referring to the past, the second part referring to the present and the third part referring to expectations regarding the future. The parent questionnaire will focus on health outcomes, HRQoL and costs.

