### Participants

The study population consists of twins and singletons born from IVF between 2003 and 2005, of whom parents have received IVF treatment in one of the five participating IVF centres in the Netherlands (Academic Medical Centre, Maastricht University Medical Centre, Radboud University Nijmegen Medical Centre, Erasmus Medical Centre and University Medical Center Utrecht). In the Netherlands, subfertility care is well-organized and centred in thirteen licensed clinics [52]. Hospitals without a licence can initiate and monitor the stimulation phase and refer to a licensed hospital for both oocyte retrieval and embryo transfer (satellite clinics) or for embryo transfer alone (transport clinics). Five of the 13 licensed centres and their collaborating transport- and satellite clinics, participate in the TwinSing study.

The *full sample *consists of all IVF twins and IVF singletons born between 2003 and 2005 of whom parents have received treatment in one of the participating centres. A total of 4,809 ongoing pregnancies were reported by these IVF centres between 2003 and 2005, of which - 3,789 singleton and 1,020 twin pregnancies. The actual size of the full sample will be somewhat lower since the reported figures are indicative; they are based on ongoing pregnancies not live births. Inclusion of an older cohort of IVF children is not considered to be valid, since the quality and results of IVF, neonatal and paediatric care have improved considerably during the last decade and since this study relies heavily on retrospective data collection, both from existing registries as well as from parents.

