**Figure 1 F1:**
[figure not shown]
**Risk stratification and sample size (figures are indicative)**.

In order to sufficiently take account of heterogeneity within the children who experienced health problems, it is expected that costs and outcome data of at least 100 singletons and 100 twin children with health problems are required in the reduced sample. Regarding children without health problems, data of 50 singletons and 50 twin children is expected to be sufficient, as variance will be considerably lower. Taking sufficiently account of missing data in all phases of data collection (5% for risk stratification, 10% for data collection up to one year of life and 20% for data collection up to five years of life), a sample size of 175 twin children with health problems, 56 twin children without health problems, 104 singletons with health problems, and 56 singletons without health problems, is required for the reduced sample.

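### The reduced-sample counts of children with health problems apply whole-cohort prevalence without the base-sample sampling fractions, so 104 singletons and 175 twins are upper bounds and the singleton minimum of 100 has almost no margin

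*Protocol article*

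**What the plan says.** Under Participants, the full sample is taken from "3,789 singleton and 1,020 twin pregnancies", with the caveat "The actual size of the full sample will be somewhat lower since the reported figures are indicative", because "they are based on ongoing pregnancies not live births".

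Under Risk stratification, "approximately 8% of the singletons will be assigned to the 'moderate risk' or 'high risk' category". All of these and 10% of the low-risk singletons enter the base sample. Twin children are expected to split 20% high, 30% moderate and 50% low risk. All high-risk twins enter, with "a random selection of 30% of the 'moderate risk' category and a random selection of 10% of the 'low risk' category".

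First-year data are collected in the base sample only. The reduced sample is then selected on those data: every child with a resolved or persistent problem, plus a random sample of the others. For that step, "resolved and persistent health problems are expected in 4.0% of the singletons and in 12.5% of the twin children".

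The sample-size paragraph after Figure 1 says that "costs and outcome data of at least 100 singletons and 100 twin children with health problems are required in the reduced sample". It allows for missing data of "5% for risk stratification, 10% for data collection up to one year of life and 20% for data collection up to five years of life" and gives 104 singletons and 175 twins with problems, and 56 of each without. The Abstract gives a base sample of 619 singletons and 659 twins and a reduced sample of 200 and 288.

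**The concern.** The sampling fractions are used to reach 619 and 659 but seem to drop out of the next step, where cases are counted. A child with a first-year problem who was not drawn into the base sample cannot enter the reduced sample. If some problems arise among low-risk children or moderate-risk twins, most of those cases are never seen, and the expected counts are too high.

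This is the article's only justification of sample size for children with problems, and the singleton figure clears its own minimum by only 4 children. The analysis also adjusts the risk classes back to their population proportions, so a low-risk case sampled at 10% stands for about ten children. The planned counts leave room for no such case.

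**Working it through.** **Inputs.** 3,789 singletons; 2 × 1,020 = 2,040 twin children; losses of 5%, 10% and 20%; class shares, sampling fractions and prevalences as stated above.

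**Base sample, reproduced**
- Singletons: 3,789 × 0.95 × (0.08 + 0.92 × 0.10) = 619.1
- Twins: 2,040 × 0.95 × (0.20 + 0.30 × 0.30 + 0.50 × 0.10) = 658.9
- Total: 1,278, as stated

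**Reduced sample, reproduced**
- Singletons with problems: 3,789 × 0.95 × 0.90 × 0.040 = 129.6, or 130
- Twins with problems: 2,040 × 0.95 × 0.90 × 0.125 = 218.0
- Without problems: 56 / 0.80 = 70 per group
- 130 + 70 = 200; 218 + 70 = 288; total 488, as stated
- After 20% loss: 129.6 × 0.80 = 103.7 and 218.0 × 0.80 = 174.4, against the stated 104 and 175

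No sampling fraction enters the case counts. Applying 4.0% and 12.5% to the base sample instead gives 619.1 × 0.90 × 0.040 = 22 and 658.9 × 0.90 × 0.125 = 74, which does not fit 488.

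**What the counts require, as population prevalences**
- 130 singletons: all cases in the 8% at moderate or high risk, a prevalence of 4.0 / 8 = 50% there and 0% in low-risk singletons
- 218 twins: all cases in the 20% at high risk, a prevalence of 12.5 / 20 = 62.5% there and 0% in moderate- and low-risk twins

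**Singletons with the fractions applied.** Let f be the share of singleton cases that are low risk, with overall prevalence held at 4.0%. Completers with problems = 103.7 × (1 − 0.9f). Low-risk prevalence = f × 0.04 / 0.92.

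| f | Low-risk prevalence | Completers with problems |
|---|---|---|
| 0 | 0% | 103.7 |
| 5% | 0.22% | 99.0 |
| 10% | 0.43% | 94.3 |
| 20% | 0.87% | 85.0 |
| 50% | 2.2% | 57.0 |

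The break-even is f = (1 − 100 / 103.67) / 0.9 = 3.9%, a low-risk prevalence of about 0.17%.

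**Cohort size.** With f = 0, 100 completers need 100 / (0.95 × 0.90 × 0.80 × 0.04) = 3,655 singletons, which is 3.5% below 3,789. The two margins are shared. If the cohort is 2% smaller, completers at f = 0 are 103.67 × 0.98 = 101.6, and the break-even f falls to (1 − 100 / 101.6) / 0.9, or about 1.7%.

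**Twins.** Completers = 174.4 × (h + 0.3m + 0.1l), where h, m and l are the shares of cases at high, moderate and low risk.

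| h / m / l | Completers with problems |
|---|---|
| 100 / 0 / 0 | 174.4 |
| 80 / 20 / 0 | 150.0 |
| 70 / 20 / 10 | 134.3 |
| 50 / 30 / 20 | 106.4 |
| 40 / 60 / 0 (equal rate in high and moderate) | 101.2 |

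Only a much flatter pattern falls well short: equal prevalence in all classes gives 59.3, which would mean that the risk criteria do not discriminate.

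The case splits in both tables are illustrations. The article gives no split by class.

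**The case against.** The strongest counter-argument is that the article names no denominator for 4.0% and 12.5%. If they meant the share of the full sample that is both drawn and affected, the fractions would already be inside them. For twins, 20% × 50% + 9% × 25% + 5% × 5% = 12.5%; for singletons, 8% × 44.25% + 9.2% × 5% = 4.0%. So the totals can be reached without zero prevalence in the subsampled classes, and it would be too much to say that they can arise in only one way. But those class rates are invented for the illustration, and nothing in the text suggests that reading. The percentages are given for the singletons and the twin children without qualification, and prevalence is the natural sense. Figure 1 is not available here and may show a split. That limits certainty, but the text still needs to stand on its own.

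A reader might infer that the design fails to deliver 100 singletons. The documents do not support that. All moderate- and high-risk singletons are sampled, 4.0% is exactly half of 8%, and 104 is attainable if essentially all cases lie in that class. Nor is the twin target shown to fail, and the 30% fraction for moderate-risk twins has no bearing on singletons.

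It is also fair that the article calls its figures indicative, admits that the cohort will be smaller, and rests the 100 on heterogeneity, not on a power calculation. A fall to the low nineties would invalidate no stated analysis. But the indicative label does not explain an omitted sampling fraction, and the 5% allowance is for risk stratification, not for pregnancies that do not end in a live birth.

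Low-risk children are also needed as children without problems and for restoring population proportions, so sampling them does not by itself contradict a zero rate. For moderate-risk twins, zero is harder to accept: a twin of 2,000 g or more with a malformation falls in that class, and malformations are a listed health outcome. For low-risk children, the article says that false negatives are minimised, not that there are none.

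**Conclusion.** The point holds as a sample-size statement that needs correcting. Taking 4.0% and 12.5% as population prevalences, 130 and 218 children with problems (104 and 175 after the last loss) are upper bounds presented as expected values. The singleton minimum of 100 is met only if no more than about 3.9% of singleton cases are low risk, with the full cohort of 3,789, or if the cohort is no more than about 3.5% smaller, with no low-risk cases. Any mixture of the two tightens both limits. The article predicts some shrinkage but does not quantify it. Twins keep about 101 to 174 completers with problems when cases are concentrated in the higher-risk classes.

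The break-even values follow from the stated inputs under that reading. The counts at other case splits rest on assumed splits. Severity is moderate: the margin is thin and undeclared, but failure is not shown.

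**What to change.** In the sample-size paragraph and the section on data collection from the first to the fifth year:

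- Say what the 4.0% and 12.5% refer to.
- Give the expected prevalence of health problems by risk class, marked as an assumption with a range.
- Recompute each class as N × sampling fraction × class prevalence × 0.9 × 0.8 and sum, with N the expected live-born children in that class after the 5% loss at risk stratification.
- Report 104 and 175 as maxima within the resulting range, and bring 200, 288 and 488 into line, including in the Abstract.
- Describe 100 singletons with problems as attainable only if nearly all cases are at moderate or high risk and the cohort hardly shrinks.

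This needs a recalculation and a few sentences. No extra children are required, and unfilled places need not be given to children without problems. The price is a less favourable stated figure.
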